**Fig. 2 Fig2:**
[figure not shown]
Study procedure and participant flow. Note. This figure shows the study procedure and the participant flow with the desired sample sizes from one assessment point to the next (estimated N). Q = questionnaire

#### Inclusion criteria

Participants will be included if they are 18 years and older and score ≥ 8 on the PHQ-9, indicating at least mild depressive complaints [31]. This cut-off score was decided upon after extensive research on the use of the PHQ in comparable research [30, 37]. The participants have to be able to read and comprehend German.

#### Exclusion criteria

Participants will be excluded if they are currently receiving psychiatric or psychotherapeutic treatment. There are no further exclusion criteria.

#### Recruitment

Participants will be invited by the online-panel “respondi AG” (ISO 20252 certified). At the first recruitment time (January/February 2021), “respondi AG” has access to approx. 80.000 active panellists via the Mingle online-access panel, whereby general representativity is controlled for through quotas. An active panellist can be anyone who is registered in a double-opt-in process and has filled out general questionnaires as well as participated in at least one survey the past 3 months, showing that they are cognitively capable of participating in online studies. No further restrictions are imposed by “respondi AG”. It is feasible that the required case number will be reached.

Participants will receive comprehensive written information about the study, after which they can give electronic informed consent. The participants will be screened according to the inclusion and exclusion criteria. Quotas will be set in place concerning gender and age-groups. Approximately 35% of the study population should be male to represent the gender distribution prevalent amongst people with depression and the age groups should be distributed as equally as possible, corresponding to the German demographic structure. These quotas will be placed by the online-panel as well as within the questionnaire algorithm.

Participants who complete the baseline and intervention assessments will be invited to the subsequent follow-ups 3 and 6 months later via e-mail. Incentive will be provided through the online-panel at each successive assessment time, respectively.

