**Methods:**

A quasi-experimental online study will be carried out to assess the effect of different intervention variables relevant for the help-seeking process. The study is conceived as a fractional factorial design. Participants will be screened for depressive complaints (PHQ-9 sum score ≥ 8) and current psychiatric/psychotherapeutic treatment. After baseline assessment the participants will be randomly allocated into one of the 24 study groups receiving different combinations of the vignette-based intervention aiming to reduce stigma and support help-seeking. Next, relevant outcome measures will be administered a second time. In a 3- and 6-month follow-up help-seeking behaviour will be measured. Gamified elements and avatar-choice techniques will be used to heighten study immersion and adherence.

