### Research agenda of the current study (stigma-II)

The present study will examine the effects of a short, informational, one-time administered intervention, aimed at influencing the intermediary process variables (i.e., continuum belief of mental illness, mental health literacy, causal beliefs, and self-efficacy to help oneself as well as seeking professional help) which in turn will reduce stigmatising attitudes and facilitate help-seeking.

The study will focus on people with at least mild depressive complaints, who are currently not receiving professional psychiatric/psychotherapeutic treatment, and live in Germany. Possible effects of the Covid-19 pandemic are assessed (e.g., adherence to regulations, mental-health burden through regulations), since it is assumed that the pandemic and lockdown-regulations had an impact on psychological well-being in general [14].

Participants of the experimental groups will receive a text-based vignette followed by a combination of online-administered interventional vignettes (either as a text and/or a video) designed to influence the five intermediary process variables described above. The participants of the control group will only be presented with the case-vignette. The primary and secondary outcomes will be measured directly pre- and post-intervention, as well as after 3 and 6 months in subsequent follow-up assessments. The primary outcome “help-seeking behaviour” will be assessed at the subsequent follow-ups. The study is designed as a quasi-experimental online study and the chosen design of experiment is the fractional factorial design [15] to adequately account for the complexity of all the possible intervention-combinations required to answer the research questions.

Prospectively, the study’s results will lead to a better understanding of the complex interplay between stigmatising attitudes and mental health care utilisation and which intermediary mechanisms play a pivotal role therewith. Moreover, the results could be used to design population wide prevention campaigns to encourage help-seeking when suffering from depressive complaints, on the one hand, and reduce stigmatising attitudes, on the other hand.

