The first part of the study will be separated into two different assessment times, both taking about 25 min to be administered, allowing for a collection of pre- and post- intervention data. During the baseline assessment participants will answer questionnaires and will be asked to participate in the second part of the study, to which they will receive an e-mail invitation 36 h later. In the second part of the study all participants will receive the online intervention (see Intervention), after which the post-assessment is administered. The participants will be informed that they will be receiving an invitation via e-mail to participate in the three- and six-month follow-up assessment.

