### Study information

#### Power & sample size

The required sample size is based on calculations for ANOVA (repeated measures, within-between interaction) expecting small effect sizes of *f* = 0.10 due to the limited intervention administration time and the online setting. A significance level of α = 0.05 and a power of *1-*β = 0.95, as well as the a priori determined 24 groups were included in the calculation. The free software G*Power [16] was used to calculate the required sample size of *N* = 840. This would mean *n* = 35 in each group. To stray on the side of safety we strive to recruit *n* = 40 for each group, a total of *N* = 960 participants, to complete the second follow-up after 6 months of intervention administration. Based on previous experience we estimate a drop-out rate of 47% between the first assessment time and the second follow-up 6 months later, we aim to recruit *N* = 1.800 at the beginning of the study (see Fig. 2).

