### Intervention

The intervention material was produced after each intermediary variable was extensively researched and refined successively after thorough review by a team of four experts. Based on the material two videos were created using the online-software Powtoon (https://www.powtoon.com/). The videos are based on the text material of the variables (1) continuum belief of mental illness and (5) self-efficacy to seek out professional help.

A first-person narrative style was chosen, because stigmatising attitudes are changed more effectively when people come into direct contact with a person suffering from depression instead of generally reading about them [13]. Furthermore, the avatar-choice technique was implemented for better identification with the intervention content [17].

During the intervention, the avatars will firstly introduce themselves and the problems they are having, self-labelling the issues as a depressive episode. Secondly, a random combination of up to five texts or videos are presented to the participants (combinations are shown in Table 1). Afterwards, a question prompts the participant to reflect on the information presented by the avatar and assess, whether they agree with the information and would act similarly to the avatar. Using this method, the avatar narrates their story, and in so doing imparts information concerning the intermediary process variables. This type of gamified intervention design was decided upon after researching ways in which people are motivated to take part in longer online experiments [19]. An avatar freely chosen and who imparts their knowledge in a comprehensive story-line narrative is important for immersion [54] and in general motivates higher study participation [17]. Also, there is evidence suggesting that both older [28] and younger adults [54] benefit from gamified interventions and that gamified e-health interventions are effective in both mental health [46] and health-related behaviour [24] contexts.

The intervention material was evaluated during cognitive debriefings [35] with 15 people suffering from depressive complaints, of whom ten had previous treatment experience. For higher standardisation a structured interview guideline was written and the interviewers instructed beforehand. The interview transcripts were used to adapt the intervention material accordingly. The intervention structure and material can be seen in the supplement to this paper*.*

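### Follow-up invitations go only to people who finish the intervention session, so collection of the primary outcome depends on completion after randomisation; inviting everyone randomised is a cheap improvement

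*Protocol article*

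**What the plan says.** The sequence has to be put together from several sections of the protocol article.

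- **Allocation.** The abstract (Methods) says: "After baseline assessment the participants will be randomly allocated into one of the 24 study groups". The section Allocation & participation timeline leaves the draw to the survey platform and does not fix its moment.
- **Session.** The e-mail invitation to the second part goes out 36 hours after baseline. Methods/design continues: "In the second part of the study all participants will receive the online intervention (see Intervention), after which the post-assessment is administered". This part takes about 25 minutes.
- **Content by arm.** For controls, the Research agenda says: "The participants of the control group will only be presented with the case-vignette". For the others, the Intervention section says that "a random combination of up to five texts or videos are presented to the participants".
- **Follow-up rule.** Recruitment: "Participants who complete the baseline and intervention assessments will be invited to the subsequent follow-ups 3 and 6 months later via e-mail".
- **Primary outcome.** Research agenda: "The primary outcome “help-seeking behaviour” will be assessed at the subsequent follow-ups". Table 2 agrees, marking help-seeking behaviour at T2 and T3 only.

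The article describes no route by which someone who is allocated but abandons the T1 session would still be invited to T2 or T3. Limitations and generalisability concedes substantial drop-out in general but does not consider whether it differs by arm.

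**The concern.** Randomisation protects a comparison as long as outcomes are sought from everyone allocated. Here the plan itself removes a group after allocation: a person who starts T1, sees arm-specific material and stops is never asked about help-seeking. Ordinary non-response can only be reduced; this loss is created by a rule and could simply be avoided.

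The rule matters if completion depends on the arm and people who break off differ in help-seeking. The first is plausible because the arms show different amounts and kinds of material. The Intervention section treats session length as something participants need motivating through, and the Discussion notes that campaigns of this kind can provoke reactance in people with depressive complaints.

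The comparison exposed is that of behaviour between randomised groups, chiefly H2c. H1, H2a and H2b concern intention, which is also measured at T0 and T1. H3 is an association with earlier treatment experience, not a randomised contrast.

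**Working it through.** **1. The plan's own sample size (Power & sample size).** Stated inputs: f = 0.10, alpha 0.05, power 0.95, 24 groups, within-between interaction. The number of measurements m and their correlation rho are not stated; I assume m = 2 and rho = 0.5. Non-centrality = N·m·f²/(1 − rho) = 840 × 2 × 0.01/0.5 = 33.6, with 23 and 816 degrees of freedom. Power is 0.954; at N = 816 it is 0.947. So N = 840 is reproduced. Drop-out: 960/(1 − 0.47) = 1,812, against 1,800 stated. The 47% already runs from first assessment to T3, so a wider invitation rule changes none of these figures.

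**2. Session content by arm (count from Table 1).** Modules shown: 0 in 1 arm, 2 in 8 arms, 3 in 10, 4 in 3, 5 in 2.

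| Factor | Mean modules, factor present | Mean modules, factor absent |
|---|---|---|
| Mental health literacy; causal belief; self-efficacy (self-help) | 3.33 (12 arms) | 2.33 (12 arms) |
| Continuum belief; self-efficacy (treatment) | 3.125 (16 arms) | 2.25 (8 arms) |

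Every main effect compares a somewhat longer session with a shorter one, but the gap is only about one module.

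**3. Size of the bias under no true effect.** All rates here are assumptions: 30% help-seeking in every arm, 15% among people who break off, and break-off d rising linearly from 5% with no module to 15% (2 points per module) or 20% (3 points per module) with five. Later non-response is taken as unrelated to arm. The rate among completers is

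R(d) = (0.30 − 0.15d)/(1 − d).

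With equal arm sizes, the pooled rate over a set of arms is R at their mean break-off.

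| Contrast | Break-off | R | Difference (points) |
|---|---|---|---|
| Two-level factor, 2 per module | 11.67% vs 9.67% | 31.98% vs 31.61% | 0.4 |
| Two-level factor, 3 per module | 15.0% vs 12.0% | 32.65% vs 32.05% | 0.6 |
| Self-efficacy (treatment), 2 per module | 11.25% vs 9.5% | 31.90% vs 31.57% | 0.3 |
| Self-efficacy (treatment), 3 per module | 14.375% vs 11.75% | 32.52% vs 32.00% | 0.5 |
| Five modules vs control, 2 per module | 15% vs 5% | 32.65% vs 30.79% | 1.9 |
| Five modules vs control, 3 per module | 20% vs 5% | 33.75% vs 30.79% | 3.0 |

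Since R(d) = 0.30 + 0.15·d/(1 − d), replacing the 15% by 45% among people who break off gives the same sizes with the opposite sign.

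**4. Yardstick.** The difference detectable with 80% power at a 30% base is about 2.80 × √[0.21 × (1/n₁ + 1/n₂)]. For the self-efficacy (treatment) factor, 8 arms against 16 at 40 each (320 vs 640), this is about 9 points, so 0.3-0.5 is roughly 4-6% of it. For control against the two five-module arms (40 vs 80) it is about 25 points.

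**5. If break-off follows content rather than length.** Module count does not capture this, and gaps between factor levels could be wider. Assume a true rate of 10-33%, people who break off seeking help at zero to half that rate, and 480 vs 480 analysed. Completion of 95% vs 90% gives 0.3-1.9 points (type I error 0.053-0.097). Completion of 95% vs 85% gives 0.6-4.1 points (0.06-0.27). With equal completion and equal selection in both levels the bias is zero.

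**The case against.** The strongest reply is that nothing in the article shows break-off to differ by arm. The avatar narrative was chosen to keep people engaged, the T1 questionnaires in Table 2 are not varied by arm, and factor levels differ by about one module. This stands: differential completion is an inference and may be slight.

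Three further points also stand. If the platform draws the group only when T1 opens, people who never return after baseline are lost before allocation and do no harm; those who stop mid-session are still lost after it. T0 holds intention, attitudes, stigma, PHQ-9 and demographics for everyone allocated, so weighting, imputation or bounds are possible. And non-response at T2 and T3, part of the expected 47% loss, stays whatever the rule.

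A reader might go further and infer that the heavier arms will look more help-seeking, that the 1.9-3.0 points apply to the main effects, or that no analysis could repair the loss. The documents support none of these. No completion data or direction is given. The larger figure belongs to an extreme contrast of three arms. The baseline data allow adjustment, though under assumptions that cannot be tested. Nor does the Intervention section clearly say that each module has its own reflection question, so extra burden of that kind should not be assumed.

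What the reply does not remove is the rule itself, which gives up outcomes that could be sought at little cost.

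**Conclusion.** The point holds as a cheap improvement, not as a flaw that must be repaired before the trial can be interpreted. By its stated rule, the plan conditions collection of the primary outcome on completing a session that follows allocation and differs by arm. This bears chiefly on H2c.

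Under the assumed 30% and 15% rates, with break-off rising linearly in module count, the spurious main effect is about 0.3-0.6 percentage points, small beside a detectable difference of about 9. It would be larger only if particular content drove people away, and its sign could go either way. All of these sizes rest on assumed rates; the article supplies none.

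**What to change.** Change the sentence in Recruitment so that every randomised participant who has not withdrawn consent is invited to T2 and T3, whether or not T1 was completed. Analyse them in their allocated group, and report T1 break-off by arm and by factor level. State the moment of the random draw. If the platform can draw the group when the T1 session opens, doing so keeps people who never return after baseline out of the randomised set.

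The cost is a few extra e-mail invitations, plus panel incentives for those who respond. Both already run through the panel, which holds the identifying data. The targets of 840, 960 and 1,800 stand. Response among people who broke off will probably be low, and later non-response at T2 and T3 remains, so the change reduces the problem without removing it.

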#### Allocation & participation timeline

The experiment-platform Unipark (https://www.unipark.com) will automatically manage allocation and each participant will be placed randomly into one of the 24 groups following an internal algorithm. Figure 2 shows the participant flow including the desired sample size at each of the four assessment times.

### Intervention

The intervention material was produced after each intermediary variable was extensively researched and refined successively after thorough review by a team of four experts. Based on the material two videos were created using the online-software Powtoon (https://www.powtoon.com/). The videos are based on the text material of the variables (1) continuum belief of mental illness and (5) self-efficacy to seek out professional help.

A first-person narrative style was chosen, because stigmatising attitudes are changed more effectively when people come into direct contact with a person suffering from depression instead of generally reading about them [13]. Furthermore, the avatar-choice technique was implemented for better identification with the intervention content [17].

During the intervention, the avatars will firstly introduce themselves and the problems they are having, self-labelling the issues as a depressive episode. Secondly, a random combination of up to five texts or videos are presented to the participants (combinations are shown in Table 1). Afterwards, a question prompts the participant to reflect on the information presented by the avatar and assess, whether they agree with the information and would act similarly to the avatar. Using this method, the avatar narrates their story, and in so doing imparts information concerning the intermediary process variables. This type of gamified intervention design was decided upon after researching ways in which people are motivated to take part in longer online experiments [19]. An avatar freely chosen and who imparts their knowledge in a comprehensive story-line narrative is important for immersion [54] and in general motivates higher study participation [17]. Also, there is evidence suggesting that both older [28] and younger adults [54] benefit from gamified interventions and that gamified e-health interventions are effective in both mental health [46] and health-related behaviour [24] contexts.

The intervention material was evaluated during cognitive debriefings [35] with 15 people suffering from depressive complaints, of whom ten had previous treatment experience. For higher standardisation a structured interview guideline was written and the interviewers instructed beforehand. The interview transcripts were used to adapt the intervention material accordingly. The intervention structure and material can be seen in the supplement to this paper*.*

### Outcome measures

Table 2 shows the variables that will be investigated at different times during the study and the instruments used to assess these. They have been classified into general psychological, intermediary process, help-seeking, stigmatisation, and context assessment measures. The final selection of the instruments, some adapted to fit the current research setting, were based on theoretical research and pre-study test results (*N* = 227), in which psychometric properties, especially of the adapted instruments, were analysed.

**Table 2 Tab2:** Questionnaires employed at the different study assessment times

Study assessments & measures	Number of items	Study time points			
		T0	T1	T2	T3
Socio-demographic					
Gender	1	X			
Month& year of birth	2	X			
Family status & partner	3	X			
Education	2	X			
Employment	2	X			
Income	1	X			
General psychological					
Subjective general health (SF-1)	1	X		X	X
Quality of life (EUROHIS-QoL Index)	8		X	X	X
Self-construal Scale (SCS)	24	X			
Subjective Socio-Economic Status	1				X
Intermediary process					
Continuum beliefs (CB_new)	12	X	X	X	X
Causal beliefs (List)	18	X	X	X	X
Mental health literacy, depression specific (D-Lit)	12	X	X	X	X
Self-efficacy to help oneself	6	X	X	X	X
Self-efficacy to seek out professional help	7	X	X	X	X
Help-seeking					
Subjective sense of illness (B-IPQ-R)	9	X		X	X
Self-identification as mentally ill (SELF-I)	5	X	X	X	X
Attitudes towards help-seeking (ATSPPH-SF)	10	X	X	X	X
Motivation behind help-seeking (ACMQ)	6	X	X		
Help-seeking intention (List)	16	X	X	X	X
Help-seeking subjective norms, attitudes and perceived control (TPB)	10	X	X	X	X
Help-seeking behaviour/ health-care utilisation	18			X	X
Stigmatisation					
Perceived public stigma and the agreement with stigma (SSMIS-public & -self-SF)	10	X	X	X	X
Social distance stigma (SDS)	7	X	X	X	X
Discrimination of mental illness	3	X	X	X	X
Sense of blame for mental illness	4	X	X	X	X
Self-stigma for seeking out professional help (SSOSH-SF)	3	X	X	X	X
Shame for being mentally ill and seeking out help	2	X	X	X	X
Emotional reaction towards a person with mental illness (ERMIS)	10	X	X	X	X
Context					
Depressive Symptoms (PHQ-9)	9	X	X	X	X
Anxiety Symptoms (PHQ-anxiety module)	7		X		
Differential diagnosis	1		X		
Previous treatment experience	3–7		X		
Perceived availability and accessibility to the health care system	1–5		X		
Covid-19 questions	4	X		X	X
	∑ = 246				

*Note.* T0 = baseline assessment, T1 = intervention assessment, T2 = follow-up after 3 months, and T3 = follow-up after 6 months. Intervention was administered online during T1

